Many studies have demonstrated that Zn supplementation enhances T cell-mediated function in Zn-deficient individuals, such as the elderly. Preliminary findings from our randomized, double-blind, placebo-controlled trial revealed that supplementation of elderly individuals with low serum Zn levels with 30 mg/d of Zn gluconate for 3 months improved serum Zn levels in majority but not all of the older adults (18). Specifically, 42% of those who completed the study in the Zn group did not reach adequate serum Zn concentrations (≥70 μg/dL) by month 3; these participants had very low serum Zn levels at baseline, with a mean ± SD of 53 ± 6 μg/dL and a range of 44–60 μg/d. Adjustment to increased Zn intake in highly Zn-deficient participants may require higher level of Zn supplementation or longer than 3 month supplementation period. Regardless, in this study we observed on average a significant increase in the percent of CD4+ T cells, and better maintained T cell function. A significant correlation between serum Zn level and T cell function, as assessed by their ability to proliferate, was also observed.

While our observational findings are supported by a small study conducted by Prasad et al. in which older adults supplemented with 45 mg/d of Zn for 12 months exhibited lower incidence of all infections including RI (19), there is an urgent need to demonstrate the efficacy of supplemental Zn to prevent pneumonia in older adults through a prospective clinical trial of adequate size and duration. As the first step toward that goal, we are conducting a 1-year double blind, placebo-controlled study to determine the effective and safe Zn supplementation dosage for NH residents. This dose will subsequently be used in a larger clinical trial to determine the effect of Zn supplementation in elderly NH patients with low serum Zn levels on the incidence of and morbidity from PNA. Additionally, results from a recent meta-analysis (20) indicated that Zn supplementation reduces the length of hospitalization in children with respiratory diseases. This further underscores the potential impact of Zn on respiratory health across different age groups.

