Clinical chemistry profile, albumin, Cu, Fe, Ferritin, CRP, and complete blood count with differential measures (CBC-diff) will be analyzed on all subjects as previously described in our Zn supplementation study (17, 18). Importantly, intestinal absorption of Cu is inhibited by Zn. Thus, chronic intake of high doses of Zn may be associated with Cu deficiency (28). This concern is the main basis for the upper tolerable limit (UL) for Zn (21). However, notably, this UL refers to chronic intake of Zn in subjects with adequate Zn level and does not preclude the use of higher doses of Zn for treatment of deficiency or diarrhea. The presence of 0.8 mg Cu in our placebo and Zn capsules will ensure no adverse effect on Cu status. Further, no serious adverse effects have been reported for long-term (up to 5 yrs) intake of up to 80 mg of Zn/day in older adults (29), who had baseline serum levels higher than those proposed in this study. Blood will be examined with a Baker 9,000 Hematology Analyzer for RBC and WBC counts and a blood smear will be used to estimate WBC differentials. This information will be used for statistical adjustment by analysis of co-variance and/or for assessment of side effects. CRP is included as it is a marker of inflammation which may impact Zn levels transiently and will be used for statistical adjustments as needed. BMI will be calculated from baseline weight and standing or knee height (in subjects who cannot stand or are contracted) (30).

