### Statistical analysis

2.9

This pilot study is a randomized dose-finding trial with the primary objective to establish optimal dose of Zn supplementation to achieve adequate serum Zn levels and estimate association between serum and cellular Zn levels. The effectiveness will be assessed based on the ability to increase serum Zn levels to adequate levels in the majority of participants (>90%) and in the shortest duration of supplementation and at the same time results in <10% of moderate or severe adverse events. Subjects will be deemed Zn adequate on the first occasion where their Zn serum level reaches ≥70 μg/dL. Subjects will not be included in the calculation of this proportion if they discontinue supplementation before reaching Zn-adequate status. Pearson correlation will be estimated between serum and cellular Zn levels. Violations of linearity will be assessed graphically, and sample product moment correlation method (34) will be used to produce two-sided confidence intervals for the estimated correlation. Analysis among dose groups will follow an intention-to-treat approach. Comparison of proportion of Zn adequate between dose groups will be tested using Fisher’s exact test with risk ratios at each time point. Continuous outcomes that have repeated measures taken at baseline, 4, 8, and 12 months will be analyzed with mixed effects linear regression which considers within-subject correlation of outcomes. We will assume linear time trends and test the dose effect by the treatment by time interaction term. Assumptions of normality and homoscedasticity will be evaluated in these models and appropriate variable transformations will be applied if needed. Age, sex, and NH site will be included in the models as covariates. A significance level of 0.05 will be used for each secondary outcome. To control for multiple testing across groups, the type I error will be reserved for the comparison between the placebo group and the selected Zn dose group. Summary statistics on any missing data will be reported, including types and patterns of missingness. Subjects with partial outcomes over time can be included in the model fit since the mixed-effects linear modeling framework allows inclusion of subjects having different numbers of repeated measures. Multiple imputation based on the multivariate normal model will be used in the case of missing covariates. Analysis will be performed using SAS (version 9.4; SAS Institute, Cary, NC).

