### Rationale for composition of treatment capsules

3.1

Based on our pilot study and review of the literature, 30 mg/d Zn is effective and safe. However, 30 mg/d was effective in improving serum Zn level to adequate in only 58% of Zn deficient participants. Further, a significant correlation between the change in Zn level and T cell proliferation was observed. We concluded that either a longer duration of supplementation with 30 mg/d or higher doses of Zn will be needed to effectively increase Zn serum to adequate levels in NH residents. Our study design will allow us to determine if a longer period of supplementation with 30 mg/d will be effective in improving Zn status in most if not all NH elderly. However, since longer than 3-months supplementation with 30 mg/d may not raise serum levels adequately, we propose to use a higher dose (60 mg/d) as well. Our rationale for selecting 60 mg/d is as follows: (1) Prasad et al. supplemented older subjects with average serum Zn level of 90 ug/dl for 1 year with 45 mg/d of Zn and noted, on average, ~12 ug/dl change in serum Zn level (13). Since we also observed about 12 ug/dl increase with 30 mg/d supplementation, yet 42% of subjects remained Zn deficient, we propose that a higher than 45 mg/d will be needed to improve Zn status in Zn-deficient elderly. (2) 60 mg/ d of Zn is a high, yet safe level of Zn for this population.

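### The adequacy comparison leaves out baseline serum Zn, a likely strong predictor already measured on everyone, so precision is forgone in a valid, adequately powered test and in the >90% dose rule

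*Protocol article*

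**What the plan says.** All references are to the protocol article.

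- **Adequacy endpoint (2.9 Statistical analysis).** "Comparison of proportion of Zn adequate between dose groups will be tested using" Fisher's exact test, with risk ratios at each time point. No covariate enters this comparison.
- **Covariates (2.9).** "Age, sex, and NH site will be included in the models as covariates". The models meant are the linear mixed models: "Continuous outcomes that have repeated measures taken at baseline, 4, 8, and 12 months will be analyzed with mixed effects linear regression". In these the plan will "test the dose effect by the treatment by time interaction term".
- **Other adjustment.** For the blood measures, 2.4.2 says "This information will be used for statistical adjustment by analysis of co-variance and/or for assessment of side effects"; CRP "will be used for statistical adjustments as needed". Section 3.3 adds albumin, if needed.
- **Randomisation (2.7).** Blocks of 6, with no stratification factor named.
- **Evidence on baseline Zn.** The Introduction says that 42% of Zn-group completers in the earlier 30 mg/d trial had not reached 70 μg/dL by month 3, and that "these participants had very low serum Zn levels at baseline" (mean 53, SD 6, range 44–60 μg/dL). Section 3.1 gives the mean change: "Since we also observed about 12 ug/dl increase with 30 mg/d supplementation".
- **Dose selection (2.1 and 2.9).** A dose qualifies on its observed proportion adequate (above 90%), reached in the shortest time, with fewer than 10% moderate or severe adverse events.

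**The concern.** Adequacy means that baseline plus change crosses a fixed line at 70 μg/dL, so baseline is part of the endpoint. With a mean rise of about 12, a participant who starts below 70 − 12 = 58 needs a better than average response to cross. The earlier non-converters fit this: their mean of 53 plus 12 gives 65, and none of them started above 60.

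Baseline serum Zn is collected on every participant (Table 1), yet the primary binary comparison ignores it. Two things are at stake. The comparison of 30 with 60 mg/d has less power than the same data could give. The raw proportion held against the 90% line also depends partly on how many low starters each arm happened to receive, and the result fixes the dose for the larger trial.

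**Working it through.** **1. The plan's own figure.** Inputs from 2.5: 58% v 90%, one-sided Fisher, α = 0.05, 80% power. Exact power is the sum, over all pairs (a, c), of Bin(a; n, 0.58) × Bin(c; n, 0.90) where the one-sided Fisher p-value is at most 0.05.

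- n = 26: 79.8%
- n = 27: 81.3%
- n = 28: 81.0%

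So 27 is the smallest n that reaches 80%, and the stated figure reproduces. (Two-sided Fisher at 27 would give 69.1%; 2.9 does not state sidedness.) For attrition, 27 / 0.80 = 33.75, so 34; 35 are planned.

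**2. How prognostic is baseline?** The article gives no baseline for converters, so this must be assumed. Non-converters were drawn from a normal distribution (53, 6) truncated to 44–60, which realised 52.5 ± 4.1. The converter mean was varied. The AUC below is the chance that a random converter started higher than a random non-converter.

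**3. Power at 58% v 90%, 27 per arm, one-sided 5%** (3,000 simulated trials per row; the adjusted test is a score test on residuals from a Firth logistic model on baseline Zn):

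| Assumed converter mean (μg/dL) | AUC | Fisher | Unadjusted score | Adjusted score | Gain from dropping Fisher | Gain from baseline Zn |
|---|---|---|---|---|---|---|
| 56.2 | 0.70 | 82.7% | 88.8% | 90.7% | 6.1 | 1.9 |
| 59.7 | 0.87 | 81.7% | 88.4% | 96.6% | 6.7 | 8.2 |
| 63.5 | 0.98 | 81.7% | 88.5% | 99.8% | 6.8 | 11.3 |

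The last row is an extreme. A separate simulation of a baseline-adjusted permutation test (600 trials per setting) gave 90–97% power against 80–84% for Fisher. Its type I error was about 4–7%; the Monte Carlo standard error at 5% is √(0.05 × 0.95 / 600) = 0.9 points.

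With both true rates at 90%, Fisher rejects about 1% of the time and the adjusted score test 4–5%. For a smaller contrast, 85% v 95%, the adjusted score test has 35%, 40% and 56% power across the three rows, against 37%, 36% and 36% for the unadjusted score test. Where baseline is only weakly prognostic, adjustment therefore gains nothing.

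**4. Noise in the proportion that the rule uses.** The total SD of an arm's proportion is √(p(1 − p)/27).

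| True rate | Total SD (points) | SD from chance baseline mix, three scenarios (points) |
|---|---|---|
| 58% | 9.5 | 3.4, 6.1, 8.6 |
| 90% | 5.8 | 1.3, 3.0, 4.6 |

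With 27 analysed, 24/27 = 88.9% fails the rule and 25/27 = 92.6% passes. An arm with a true rate of 90% passes with probability P(X ≥ 25) = 48.5%. Part of that uncertainty comes from baseline mix and could be reduced.

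**The case against.** The strongest case against is that nothing here is wrong. Sizing and analysis both name Fisher's test, it is valid with few events, and chance baseline imbalance is already inside its type I error. All of that stands.

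Four stronger readings are tempting, and the documents support none of them.

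- **That the trial loses power it was promised.** It does not. Fisher stays at about 82–83% in every row of the table, and 6 to 7 points of the apparent gain come from Fisher's conservatism, not from baseline Zn.
- **That baseline is shown largely to decide conversion.** Only non-converters are described, and only at month 3. This trial measures at 4, 8 and 12 months and counts the first value at or above 70. The Introduction itself says that very deficient participants may need longer than 3 months, so the dependence may weaken.
- **That the models adjust only for age, sex and site.** Sections 2.4.2 and 3.3 announce further adjustment, and the mixed models already hold the baseline value as a repeated outcome. The gap concerns the binary endpoint alone.
- **That chance imbalance could readily choose the dose.** If the between-arm difference in mean baseline has an SD of about 1.65 μg/dL (assumed mean 58.6, SD 6.1, truncated below 70), one arm's mean has an SD of 1.65/√2 = 1.17. A 3 μg/dL shift in one arm is then 3/1.17 = 2.6 SD, which is rare. Even so, a favourable shift of that size takes the 30 mg/d rate from 58% only to 66–72%, far from 90%. The effect matters only for an arm whose true rate lies near the line.

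A last objection also stands: the dose is selected on the raw proportion and not on Fisher's p-value, so changing the test alone would leave the rule exposed.

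**Conclusion.** The point holds as forgone precision on the primary binary endpoint, not as an error. The planned test is valid and meets its 80% target when one-sided (81.3% at 27 per arm). Adjusting for baseline serum Zn, with a test less conservative than Fisher's, would bring power to roughly 90–97%; about 2 to 11 points of the gain are due to baseline Zn itself. Chance baseline mix supplies an SD of 1.3 to 4.6 of the 5.8 points of sampling SD in an arm at a true 90%.

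The sizes rest on an assumed baseline distribution for converters, on the month-3 pattern carrying over to this trial, and on 58% v 90% being the true rates. The direction rests on the article's own report that all non-converters started at or below 60 μg/dL. The change is worth making because the data are already collected. Leaving it out would not invalidate the pilot.

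**What to change.** Amend the analysis text in 2.9, or set it out in the SAP before unblinding:

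1. Compare adequacy between dose groups with a logistic model that includes continuous baseline serum Zn and a small-sample correction such as Firth's. Report the standardised risk difference and risk ratio, with a permutation p-value.
2. Keep Fisher's exact test as a sensitivity analysis.
3. When the >90% rule is applied, report each arm's proportion standardised to the pooled baseline Zn distribution, with a confidence interval, beside the raw proportion. Without this step the dose rule gains nothing from the adjustment.

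The cost is a little more analysis work, with no new data and no change to randomisation. The real downside is model dependence. At a 90% rate, about 27 × 0.10 = 2.7 failures are expected in the 60 mg/d arm, so the model must stay simple, and the small-sample correction and the permutation p-value are needed.

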### Design

2.1

We are conducting a one-year long RCT to determine an effective and safe Zn supplementation dosage for elderly NH residents with low serum Zn levels (< 70 μg/dL), this threshold is recommended by Institute of Medicine, Panel on micronutrients (21) and others (22). Two Zn dosages, 30 or 60 mg/d, will be tested. The primary objectives are to establish the optimal dose of Zn supplementation required to achieve adequate serum Zn levels and estimate the correlation between serum and intracellular labile Zn levels. The secondary objectives are to assess adverse events and immune outcomes and collect data on PNA to design a larger clinical trial effectively. The selection of the dose will be determined by the combination of time and dosage that exceeds threshold for achieving adequate serum Zn levels in the majority of subjects (>90%) while remains below designated threshold for incidence of the side effects (<10% moderate or severe side effects, see below).

A total of 105 male and female elderly subjects (≥65 y) with low serum Zn (<70 μg/dL) will be enrolled from a NH within 1 h driving distance from Boston (from an estimated 16 NHs, ~900 residents) and be assigned to one of the 3 groups. Group 1 will serve as control and will receive a capsule containing ½ Recommended Dietary Allowance (RDA) of all the essential micronutrients (MN), including 5 mg of elemental Zn (1/2 RDA MN); group 2 will receive a capsule containing ½ RDA MN including 30 mg/d elemental Zn, and group 3 will receive a capsule containing ½ RDA MN including 60 mg/d elemental Zn. Zn is provided as Zn gluconate. The overall study design and number of subjects is shown in Figure 1 and the frequency of data collection is shown in Table 1.

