### Randomization, allocation concealment, and blinding

2.7

Subjects will be assigned to each arm via block randomization with a block size of 6. The randomization will be done via the built-in random number generator included in the study database and data capture system, REDCap. Placebo and Zn supplements will be provided in identical capsules to maintain double blinding. The database manager will retain the randomization code. Other members of the study team, including the Co-PIs, will be blinded to treatment assignments. The placebo and Zn capsules have been developed to have identical appearance to ensure blinding of the treatments.

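### Section 2.9 does not give the randomised arms a common baseline mean in the mixed model; fitted in the usual way, the treatment-by-time test is valid but less precise than the data allow

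*Protocol article*

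**What the plan says.** Section 2.9 of the protocol article sets out the model for the continuous outcomes:

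- Outcome vector: "Continuous outcomes that have repeated measures taken at baseline, 4, 8, and 12 months will be analyzed with mixed effects linear regression". Baseline is thus one of four repeated outcomes.
- Time form and test: "We will assume linear time trends and test the dose effect by the treatment by time interaction term".
- Covariates: "Age, sex, and NH site will be included in the models as covariates". The baseline value of the outcome is not listed.
- Covariance: described only as "mixed effects linear regression which considers within-subject correlation of outcomes". No structure or correlation is given.
- Error level: "A significance level of 0.05 will be used for each secondary outcome". Sidedness is not given. The type I error is kept for placebo against the selected zinc dose.

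Section 2.7 says: "Subjects will be assigned to each arm via block randomization with a block size of 6". Baseline blood is therefore compared between randomised groups before supplementation can act. Section 2.4.2 mentions analysis of covariance, but for blood counts, with CRP for adjustment as needed, and not for the baseline value of each outcome. Nothing in the article says whether the arms share one baseline mean.

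**The concern.** A treatment-by-time test is ordinarily fitted with both main effects. With baseline at time 0 in the outcome vector, the treatment main effect is then a free difference between arms at baseline. Under randomisation the true value of that difference is zero. Estimating it means that a chance imbalance at baseline carries into the slope comparison without the shrinkage that the within-subject correlation would justify. Age, sex and site do not restore the missing constraint.

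What is at stake is precision for the T-cell measures, copper and cellular zinc, compared on about 27 to 35 participants per arm. At that size the chance difference in baseline means has a standard error of √(2/35) = 0.24 to √(2/27) = 0.27 standard deviations, so some imbalance is likely over several outcomes. The secondary data are also meant to inform the design of the larger trial (section 2.1).

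**Working it through.** **The plan's own figure.** The only calculated figure is 27 per group for 58% against 90% conversion, by a one-sided Fisher's exact test at 0.05 (section 2.5). Exact enumeration gives power of 79.8% at 26 per group and 81.3% at 27, so the figure reproduces. It concerns the binary endpoint and does not involve the mixed model.

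**Inputs for the mixed model.** From section 2.9: visits at t = 0, 4, 8 and 12 months, linear time, and the treatment-by-time term as the test. Assumed, because the article does not give them: complete data, equal arms, unit variance, and compound symmetry with correlation r, so V = (1 − r)I + rJ.

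**Information on the slope difference, per pair of arms and up to a common factor.** Σt² = 224 and Σt = 24, so (Σt)² = 576.

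- Arm-specific baseline means: [224 − 576/4]/(1 − r) = 80/(1 − r).
- One common baseline mean: [224 − 576r/(1 + 3r)]/(1 − r).

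The factor 1/(1 − r) cancels. The variance ratio, common over arm-specific, is 80/[224 − 576r/(1 + 3r)].

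| r | Bracket, common baseline | Variance ratio | Variance cut | Power with common baseline where arm-specific has 80% |
|---|---|---|---|---|
| 0.3 | 133.1 | 0.601 | 40% | 95% |
| 0.5 | 108.8 | 0.735 | 26.5% | 90% |
| 0.7 | 93.9 | 0.852 | 14.8% | 86% |
| 0.8 | 88.5 | 0.904 | 9.6% | 84% |
| 0.9 | 83.9 | 0.954 | 4.6% | 82% |

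The power column assumes a two-sided 0.05 test: power = Φ[(1.960 + 0.842)/√ratio − 1.960]. In sample-size terms, 27 per arm with a common baseline matches 27/0.735 ≈ 37 per arm with arm-specific baselines at r = 0.5, and 27/0.852 ≈ 32 at r = 0.7.

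**Other covariance structures.** The same variance comparison gives:

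- First-order autoregressive, correlation 0.5 to 0.9 between adjacent visits: a cut of 46.6% down to 13.6%.
- Random intercept and slope (intercept variance 0.3 to 0.8, total baseline variance 1, slope SD 0.05 to 0.3 per four-month interval, intercept-slope correlation −0.4 to 0.3): a cut from about 0% to 45%.

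**Serum zinc.** The design section says that "elderly subjects (≥65 y) with low serum Zn (<70 μg/dL) will be enrolled", which truncates the baseline. Take baseline as the lowest 29% of a normal distribution, 29% being the prevalence of deficiency given in section 2.2. Its variance falls to 0.26 of the untruncated value. With compound symmetry before truncation, the cut is 17.0% at r = 0.3, 9.5% at 0.5, 4.6% at 0.7 and 2.8% at 0.8.

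**Baseline as a covariate instead.** If months 4, 8 and 12 are the outcomes and treatment-by-time is tested beside a free treatment main effect, only the spread of the three visits about month 8 carries information: 16 + 0 + 16 = 32. The information is 32/(1 − r) against 80/(1 − r), so the variance is 80/32 = 2.5 times that of the usual four-visit model, at every r.

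**The case against.** The strongest reply is that section 2.9 never says a treatment main effect is fitted. A model with a common baseline mean also has baseline in the outcome vector and reads the effect from treatment-by-time, and a condensed article may leave that detail to a fuller document. This stands in part. Arm-specific baselines are the usual reading of the text, not its words. But the article does fix the outcome vector, time form, tested term and covariates, and the ordinary fit of that description leaves the constraint out. If a common baseline was intended, the same sentence would settle it.

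The second reply is that the usual model is a standard, valid analysis. This stands in full. If the linear trend holds it is unbiased, and in simulated trials of three arms of 27 (1,500 per scenario, compound symmetry) type I error was 4.5-5.3% for both models. The outcomes concerned are mostly secondary, in a pilot that claims no power for them.

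A reader might infer two stronger points that the article does not support:

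- That the plan throws the baseline data away. It does not: baseline is the first point of each participant's trend and contributes through the within-subject covariance. Only the equality of the arm means goes unused.
- That every continuous outcome loses 15-27%. That band belongs to compound symmetry at correlations of about 0.5-0.7. The article gives no correlation, and serum zinc falls below the band because of its entry limit.

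**Conclusion.** The point holds as a matter of precision, not of validity. As section 2.9 is ordinarily fitted, the comparison of placebo with the selected dose on continuous outcomes is less precise than the same data allow. The size rests on an unreported covariance, so only the range can be defended, and no single figure applies to all outcomes. It also rests on the linear trend that section 2.9 itself assumes, and on a treatment main effect being in the model. The rule for selecting the dose, the Fisher comparison and the sample size rest on proportions and do not change. This is a free improvement, not the correction of an error.

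**What to change.** In section 2.9, state that the mixed model uses one baseline mean common to all randomised arms, with no treatment main effect at time 0, and keeps the treatment-by-time term, from which placebo is compared with the selected dose.

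If months 4, 8 and 12 are instead analysed with the baseline value of the same outcome as a covariate, the test should be the arm difference at the post-baseline visits, or their average. Treatment-by-time beside a free treatment main effect should not be the test there, since it would lose far more precision than the change is meant to gain.

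The cost is one sentence. It needs no new visits or measurements, and under randomisation the common-baseline constraint introduces no bias.
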